#### Study 1: Assess sensitivity and validity of the new social cognition instruments.

To assess if the newly developed instruments can differentiate between the presence of frontal social cognitive pathology and the absence of such pathology, and to assess the construct validity of these new instruments, the newly developed instruments, as well as existing social cognition measures and general cognitive measures, will be administered to participants. See Table 1.

**Table 1 pone.0324517.t001:** Assessment instruments Study 1 New SC instruments.

Assessment	Construct
**General information**	
Demographics	Age, sex, educational level
Medical information	Diagnosis, time since diagnosis, dementia type (including genetics), imaging data (MRI, PET).
Driving experience questionnaire – self	Driving experience (e.g., age obtaining driving license, lifelong number of driven kilometres, driving behaviour)
Driving experience questionnaire – proxy	Proxy-rated driving behaviour
**New social cognition measures**	
Nummenmaa Emotion Experience Test (NEET)	Bodily experience of emotions
Empathy Task of Identifying emotions and Feeling with another (ETIF)	Empathy; identifying emotions and feeling with another
Groningen Theory of Mind Battery	Cognitive and affective Theory of Mind, verbally as well as non-verbally
**Existing social cognition measures**	
Facial Expressions of Emotions – Stimuli and Test (FEEST)	Facial emotion recognition
Social Norms Questionnaire (SNQ-NL)	Compliance with and understanding of social norms
Toronto Alexithymia Scale (TAS-20)	Alexithymia
**General cognitive measures**	
Mini Mental State Examination (MMSE)	Cognitive screener
15 Words Test (15WT)	Verbal memory
Trail Making Test (TMT)	Psychomotor speed, visual attention, and mental flexibility
Digit span	Working memory
Symbol Digit Modalities Test (SDMT)	Mental speed
Letter fluency	Language, phonological fluency, executive control
Verbal fluency	Language, semantic fluency
Dysexecutive Questionnaire (DEX) – self	Dysexecutive syndrome and behavioural changes, self-reported
Dysexecutive Questionnaire (DEX) – proxy	Dysexecutive syndrome and behavioural changes, proxy-reported

The Nummenmaa Emotion Experience Test (NEET) is designed to measure bodily experience of emotions, i.e., if someone is able to experience and identify in which parts of their body, they experience specific emotions. The concept of the test is derived from research of Lauri Nummenmaa [19] who constructed emotion-specific maps of bodily sensations, using a topographical self-report method. For the NEET, participants are presented with an empty map of a body, accompanied by a specific emotion. The test includes the following eleven emotions: anger, fear, disgust, happiness, sadness, surprise, love, contempt, pride, shame, and envy. Participants are instructed to take time to evoke this emotion within themselves, by thinking about a situation in which they have felt this emotion or would possibly feel this emotion. Then, they must click on the body parts in which they experience that specific emotion, resulting in the appearance of a red glow in that body part. The map includes the following body parts: 1) head (including face); 2) throat; 3) chest; 4) arms; 5) hands; 6); abdomen; 7) pelvic area; 8) legs; and 9) feet. Before starting the test, participants are provided with two practice items for the emotions ‘nervous’ and ‘disappointed’.

The Empathy Task of Identifying emotions and Feeling with another (ETIF) is inspired by the Empathic Accuracy Task paradigm of Zaki and colleagues [20]. To construct the ETIF, eleven male and female Dutch-speaking persons of different ages were recruited and asked if they would like to participate in the development of a new test for measuring empathy. Before filming these ‘targets’ were asked to recall a specific autobiographical event, in which they experienced one of the six basic emotions (i.e., happiness, fear, anger, surprise, disgust, or sadness). They were asked to write a short summary of each event they could recall, and to rate its overall emotional intensity on a 5-point scale, ranging from 1 (‘did not feel the emotion at all’) to 5 (‘experienced the emotion very strongly’). Only events with a rating of 4 or 5 were filmed. Before filming, targets were instructed to take their time recalling the situation to reinstate the affective state they had felt during the event. When talking about the situation in front of the camera, they were not allowed to make specific references to their affective state (i.e., ‘sad’ or ‘happy’), but they were allowed to describe their bodily symptoms (‘shaking hands’, ‘lump in my throat’). All targets were filmed from the upper chest upwards, in front of a white wall, for standardisation purposes. Each clip lasted between 16 seconds and 70 seconds (mean = 41.8, SD = 17.2). For each emotion, two clips were selected for the test, one including a woman and one including a man. During the administration of the ETIF, videos are presented full screen. After watching each video, participants are asked the following questions: 1) How do you think the person in the videoclip felt during the event? 2) How do you think the person in the videoclip felt while *talking about* the event? 3) Which of these emotions fits best to describe how the person in the videoclip felt while talking? Happy, surprised, fearful, angry, sad, disgusted, or neutral. 4) Does the videoclip evoke an emotion or a feeling in you? And if the participant answers this question with ‘yes’, it is asked 5) what emotion or feeling is that? With regards to scoring, only question 3 and question 5 are scored, with one point for a correct or appropriate answer. The answers to question 3 form the subscale ‘Identifying another’s emotions’, while the answers to question 5 form the subscale ‘Feeling with another’. Each subscale has a maximum score of 12, and both subscales combined form a total Empathy score.

The Groningen ToM battery consists of four parts including items of different already existing tests for measuring ToM. Of each included test, the six most ‘sensitive’ items were selected, based on which items showed the largest significant difference between a group of patients, and healthy controls. The first part of the Groningen ToM battery consists of six items of the Hinting Task [21]. A maximum of twelve points, two points per question, can be obtained on this part. Two points will be awarded if the participant immediately gives a correct answer, and one point will be awarded if the participant answers correctly after receiving a hint. No points will be awarded if the participant does not answer correctly. The second part of the Groningen ToM battery consists of six, slightly adapted, items of the Faux Pas [22–24]. The following questions are asked in the Faux Pas test: 1) Did anyone say something they should not have said or something awkward? If the participant answers with ‘yes’, question 2 and 3 are asked: 2) who said something they should not have said or something awkward? and 3) why should he/she not have said it or why was it awkward? Regardless of the answer on question 1, the following two questions are always asked: 4) How do you think (the person to whom something awkward was said) felt? and 5) How do you think (the person that said the awkward thing or something he/she should not have said, or a third person) felt? For this part, a maximum of twelve points can be obtained for correctly identifying whether there is a faux pas and why there is a faux pas, and a maximum of twelve points can also be obtained for correctly identifying how the persons in the stories feel. The third part of the battery includes three items of the Story-based Empathy Task (SET) [25] in which the ability to infer other’s intentions (cognitive ToM) is assessed, and three items of the SET in which the ability to infer other’s emotions (affective ToM) is assessed. Per item, participants are awarded one point for correctly describing how they think the story ends, and another point for choosing the right ending out of three options. Six points can be awarded for the cognitive ToM items, and six points can be awarded for the affective ToM items, resulting in a maximum of twelve points for this part. The last part of the Groningen ToM battery includes six adapted items of the Cartoon test [26]. The adaptations made to the Cartoon test are the addition of one or two extra questions as a subtle hint, and the use of a different scoring model. In the original version people are awarded 0–3 points per item, depending on the elements named in their answer. In our version, people are awarded two points for an answer that is immediately correct, and one point for an answer that is correct after the additional question(s) is/are asked. Zero points are awarded when someone is unable to give a correct answer. Participants can obtain a maximum score of twelve in total, including six points for ToM items, and six points for non-ToM items.

#### Study 2: Investigate relationship between social cognition and risk-taking behaviour (ecological validity).

To investigate the relationship between social cognition and risk-taking behaviour, new and existing social cognitive measures will be administered to participants. Furthermore, risk-taking behaviour will be assessed with the Action Selection Task (AST) from the Institute of Road Safety Research (SWOV), the newly developed Risk-Taking Survey, and the newly developed Risk-taking in Traffic Task (RiTT), see Table 2. To account for the influence of other cognitive aspects, all general cognitive measures from Study 1 will also be administered in Study 2.

**Table 2 pone.0324517.t002:** Assessment instruments Study 2 Association SC and risk-taking behaviour.

Assessment	Construct
Study 2 also includes all assessments that are conducted in Study 1	
Risk-taking in Traffic Task (RiTT) (new)	Risk-taking behaviour in a driving simulator task
Risk-taking survey (RTS) (new)	Risk-taking behaviour in daily life
Action Selection Task (AST)	Risk-taking behaviour in static traffic situations
Mirror Test	Mimicry

The Risk-taking survey measures the degree to which a person can accurately identify situations that contain a possible risk for themselves or for another person. It consists of 30 *Yes-No* questions to be completed by the participant after a standardized instruction by the examiner. The instruction is as follows: “Here you are provided with a list of behaviour of people. Is it in your opinion *dangerous* or *risky* to do these things? Please check yes or no. With regard to *risky*, think of something that has a considerable chance to have adverse consequences, immediately, or in the longer term, and what you, therefore, should better not do.” Examples of questions are *“Is it risky or dangerous to sit in the backseat of a car, without your seat belt fastened?”* (Yes), or *“Is it risky or dangerous to eat a pastry with whipped cream on a birthday, in the presence of young children?”* (No).

With the RiTT, risk-taking behaviour in traffic situations will be measured in a driving simulator, that is positioned on a moving platform. The simulator operates in automatic gearbox mode. First, the participant will complete two practice scenarios. The first practice scenario focuses on learning how to accelerate and how to manage the steering wheel. The scenario takes place in a rural environment, on a winding road. The second practice scenario is focused on learning how to adapt driving speed, and learning how to break, while also focusing on traffic and traffic rules. This again takes place in a rural environment, but now the participant will encounter cross-roads, for which different priority rules apply. If needed, one or both practice scenarios can be repeated. After the practice scenarios, the risk-taking scenario will be completed. In this scenario, the participant is driving through rural, but also urban, environments. As an instruction, the participant has been told that they are late for an appointment, and that they must get to their appointment as soon as possible. They are also told that they still must comply with traffic rules and that they should drive as they would drive in real life. During the route that the participant must drive, different situations occur in which there is a possible risk for the participant him-/herself, for others or for both self and others. There are also situations that are comparable to the risk situations, but do not include a risk.

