1)Assess sensitivity of new performance-based SC measures (including emotion experience and empathy) ◊ Study 12)Assess construct validity of the new performance based SC measures ◊ Study 13)Assess the relationship between social cognition and unsafe risk-taking behaviour (measuring ecological validity of the new SC tests), and investigate if this relationship is generic (by including patients with brain injury affecting frontal networks) or specific (by including patients with non-bvYOD variants, for whom no SC impairments or risk-taking behaviour are expected) ◊ Study 2

As a result of this study, we hope to introduce new, sensitive neuropsychological instruments which may aid in a more timely diagnosis of bvYOD and a better identification of social behavioural symptoms in general.

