#### Study 2 Relationship between social cognition and risk-taking behaviour (ecological validity).

The relationship between SC test performance and actual social behaviour (ecological validity), specifically risk-taking behaviour, will be investigated by analysing the relationship between the SC tests and the risk-taking measures with parametric or non-parametric correlation analyses in the different groups (bvYOD, non-bvYOD, brain injury, healthy controls). A significant correlation will demonstrate an association between social cognition and risk-taking behaviour and therefore, be indicative ecological validity. By looking specifically at the association between SC and risk-taking behaviour in patients with frontal brain injury, it will be assessed whether this relationship is generic for all patient groups with SC impairments. Furthermore, by assessing this relationship specifically in patients with non-bvYOD, for whom no SC impairments or risk-taking behaviour are expected, it will be assessed whether this relationship is specific.

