## Discussion

To the best of our knowledge, the YOD-RiSoCo study will be the first to investigate the relationship between aspects of social cognition and risk-taking behaviour in a broad sample of patients with bvYOD, non-bvYOD, patients with brain injury affecting frontal networks, and healthy controls. Furthermore, we hope the study will lead to new valid instruments for measuring aspects of social cognition for which currently valid instruments are lacking.

First, the YOD-RiSoCo study will result in new sensitive and valid measures for aspects of SC, such as bodily emotion experience, and empathy. These measures will hopefully facilitate a better identification and deeper understanding of social cognitive difficulties in patients with behavioural variants of young-onset dementia. As patients with these bvYOD subtypes present with changes in social behaviour, related to SC impairments, the new instruments will hopefully lead to better recognition of these first symptoms, resulting in a timelier diagnosis.

Furthermore, by investigating the relationship between social cognition and risk-taking behaviour, the association between SC impairments and problematic social behaviour, such as risk-taking behaviour, will be assessed. Identifying risk-taking behaviour is important, as it can have detrimental consequences for patients themselves, but also for other people that might be unintentionally affected by risk-taking behaviour. If a relationship between SC and risk-taking behaviour is found in this study, guidelines regarding fitness to drive in patients with bvYOD or brain injury affecting frontal processes should be reviewed and revised to be more applicable to patients with SC impairments and social behavioural change.

In conclusion, the results of the YOD-RiSoCo study will contribute to a more comprehensive understanding of social cognition and risk-taking behaviour in patients with young-onset dementia, which may speed up the diagnostic process of young-onset dementia, allowing timely provision of appropriate counselling and care for patients and their close others.

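### The Risk-taking survey scores recognition of risk, yet Study 2 counts it as a risk-taking measure when concluding on ecological validity

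*Protocol article*

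**What the plan says.** All references are to the protocol article.

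- **Study 2 instruments section.** It states that "risk-taking behaviour will be assessed with the Action Selection Task (AST) from the Institute of Road Safety Research (SWOV), the newly developed Risk-Taking Survey" and a driving-simulator task, the Risk-taking in Traffic Task (RiTT).
- **Table 2.** The survey's construct is "Risk-taking behaviour in daily life". The RiTT and the Action Selection Task (AST) are labelled as risk-taking behaviour in a simulator and in static traffic situations.
- **Text below Table 2.** The survey "measures the degree to which a person can accurately identify situations that contain a possible risk for themselves or for another person". Its instruction opens "Here you are provided with a list of behaviour of people" and asks for a yes or no on whether doing each thing is dangerous or risky. Two of the 30 items are shown, each with its keyed answer.
- **Statistical analysis, Study 2.** SC tests are correlated with the risk-taking measures in each of four groups in order to examine actual social behaviour. "A significant correlation will demonstrate an association between social cognition and risk-taking behaviour and therefore, be indicative ecological validity".
- **Discussion.** If a relationship is found, "guidelines regarding fitness to drive in patients with bvYOD or brain injury affecting frontal processes should be reviewed and revised".

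**The concern.** The survey's label and its description name different constructs. Judging correctly that an act is risky is not the same as refraining from it. The article's own rationale depends on that difference: the Background proposes that patients take risks because they do not feel emotions such as fear as a warning. On that account a patient could recognise a risk and take it anyway.

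The analysis section draws no such distinction. A correlation between an SC test and the survey meets its wording for ecological validity exactly as a correlation with simulator driving would. The conclusion about actual behaviour, and the implication in the Discussion, could then rest on an association between two judgement tests.

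**Working it through.** The plan states no figure on this point, so the check sets its statements side by side and then counts how much of the analysis is affected.

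**Step 1. What the survey asks.**

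| Source | What it indicates |
|---|---|
| Table 2 | The participant's risk-taking in daily life |
| Description | Accuracy in identifying risky situations |
| Instruction | The participant's opinion on whether behaviours of people are risky |
| Two example items | Keyed yes/no judgements on sitting unbelted in the back of a car and on eating a pastry at a birthday |

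Three of the four sources describe recognition or judgement. Only the Table 2 label says behaviour. Nothing shown asks whether or how often the participant does any of these things.

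**Step 2. What a correlation with it would show.** One of the new SC tests, the Groningen Theory of Mind battery, includes faux pas stories in which the participant judges whether a character said something inappropriate. The survey asks for judgements on described conduct as well. A correlation between the two would link one judgement score to another. Under the analysis section it would still count as ecological validity.

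**Step 3. How much of the analysis is affected.** The inputs are:
- risk measures: 3 (RiTT, survey, AST);
- groups: 4 (bvYOD, non-bvYOD, brain injury, healthy controls);
- SC instruments: 6 if "new and existing social cognitive measures will be administered to participants" covers all those in Table 1 (NEET, ETIF, Groningen battery, FEEST, SNQ-NL, TAS-20), or 3 if the aim in the Background, "measuring ecological validity of the new SC tests", limits it to the new ones.

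Assume one score per instrument. The number of correlations is SC instruments × risk measures × groups.
- Six instruments: 6 × 3 × 4 = 72, of which 6 × 1 × 4 = 24 involve the survey.
- Three instruments: 3 × 3 × 4 = 36, of which 3 × 1 × 4 = 12 involve the survey.

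The share is 24/72 = 12/36 = one third on either reading. These counts are derived here; the article does not state them.

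**The case against.** The strongest reply is that this is a small labelling slip. The survey is one of three measures. The RiTT observes driving in a simulator, and Table 2 gives the AST a behavioural construct. The study's main outcome lies in Study 1, and the Discussion's remark is conditional and not tied to the survey. All of this is true and limits the point. It does not remove it, because the analysis section gives the survey the same evidential weight as the other two, and a full protocol or analysis plan would not undo the contradiction in the article.

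Two stronger readings are tempting, and the document does not support them.

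- **That any single significant correlation among dozens would suffice, uncorrected.** The general Statistical analysis section promises Bonferroni-Holm or another appropriate correction for multiple comparisons, so false-positive rates for an uncorrected analysis do not describe this plan. Nor is 72 a floor, since the aim's wording gives 36. The correction family is not spelled out, but a condensed article commonly leaves such detail to the full document.
- **That Study 2 should be reduced to one test of one SC score against one risk score in all 80 participants.** The groups are expected to differ in both SC and risk-taking, so differences between group means alone could produce a pooled correlation. Such a test would also bypass the within-group question of whether the relationship is generic or specific. The absence of a single primary pair in Study 2 is not in itself an error.

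**Conclusion.** The point holds as an internal contradiction with a consequence. The survey is labelled as behaviour and described as recognition, and the analysis rule lets it support a conclusion about behaviour. It affects one of three risk measures and one third of the planned SC-risk correlations. It does not invalidate the other two thirds.

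This rests on three assumptions:
- the 28 items not shown follow the same instruction as the two examples;
- the AST and RiTT measure what Table 2 says (the article does not describe the AST task further);
- each instrument contributes one score per group, which affects the counts but not the contradiction.

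If the survey does contain items on the participant's own conduct, the description needs correcting instead of the label.

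**What to change.** 1. In Table 2, relabel the survey's construct as risk recognition or risk judgement, and make the sentence that lists the risk-taking measures agree with it.
2. Analyse the survey separately and report it as secondary: a correlation with it shows that social cognition relates to judging risk.
3. In the Study 2 analysis, base the ecological-validity conclusion on the RiTT and the AST, within groups as planned, with the promised correction applied across those pairs. With one score per instrument that is 6 × 2 × 4 = 48 correlations, or 3 × 2 × 4 = 24 for the new tests only.
4. Tie the Discussion's fitness-to-drive implication to those results.
5. Use the proxy-rated driving questionnaire, already listed in Table 1, as supportive evidence from real life.

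The cost is a table label and a few sentences, with no new data. The downside is that fewer associations can be claimed as ecological validity. Because the survey is the only risk measure labelled as daily-life behaviour, the remaining claim is confined to traffic situations. Recruitment is planned until the end of 2026, so the change can be made before the analysis.
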